# The effect of virtual specialist conferences between endocrinologists and general practitioners about type 2 diabetes: study protocol for a pragmatic randomized superiority trial

**DOI:** 10.1186/s13063-022-06961-y

**Published:** 2022-12-28

**Keywords:** Virtual conferences, General Practitioners: General practice, Randomized trial, Type 2 diabetes

## Abstract

**Background:**

To support the primary care sector in delivering high-quality type 2 diabetes (T2D), literature reviews emphasize the need for implementing models of collaboration that in a simple and effective way facilitate clinical dialogue between general practitioners (GPs) and endocrinologists. The overall aim of the project is to evaluate if virtual specialist conferences between GPs and endocrinologists about patients living with T2D is clinically effective and improves diabetes competences and organization in general practice in comparison to usual practice.

**Methods:**

A prospective, pragmatic, and superiority RCT with two parallel arms of general practices in the Municipality of Aarhus, Denmark. All general practices are invited (*n* = 100). The intervention runs for 12 months and consists of four virtual conferences between endocrinologists and an individual general practice. Before the first conference, an introductory webinar teaches GPs about how to use an IT-platform to identify and manage T2D patients. The main analysis (month 12) concerns the difference between the intervention and control arm. It is expected that the virtual conferences at the patient level will improve adherence to international recommendations on diabetes medication for T2D patients and improve the risk profile with a reduction in glycated haemoglobin, blood pressure, and cholesterol. The study design allows for identifying a significant difference between the intervention (*n* = 15) and control group (*n* = 15) regarding the three primary clinical outcomes with a power of 0.8870–0.9941. At the general practice level, it is expected that general practitioners and practice staff in the intervention group will improve self-reported diabetes competence and organization. The control arm will get the intervention when the primary intervention ends (months 12–24), and the intervention arm transitions to a maintenance phase.

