### Assignment of interventions

Block randomization is performed at the general practice level. General practices will be randomized in a 1:1 ratio to either the intervention or the control group by a statistician, according to a computer-generated list, independent of the measurement team. Randomization included stratification by number of full-time GPs and geographic location. The latter because general practices located in the centre and periphery of the municipality of Aarhus differ in patient demographics. A hospital secretary will be in charge of enrolment of participants.

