### Outcomes

#### Clinical outcomes

Table 2 shows the primary and secondary patient outcome measures. The primary patient outcomes are the percentage of patients with T2D and three types of co-morbidities on appropriate diabetes-related medication: ischemic heart disease and/or stroke; micro- or macro-albuminuria; and LDL > 2.5 mmol/L. To account for multiplicity, we use the Bonferroni correction method to adjust the *p*-values of the three primary clinical outcomes. The Bonferroni correction sets the significance cut-off at α/n [36], which means we only reject the null hypothesis of a primary clinical outcome if the *p*-value is less than 0.0167 (i.e., 0.05/3).

**Table 2 Tab2:** Overview of primary and secondary outcomes measures

Aspect	Outcome measure
Primary clinical outcome measures	Percentage of patients with T2D and ischemic heart disease and/or stroke being treated with glucagon-like peptide 1 receptor agonists (GLP1-RA) and sodium glucose cotransporter 2 (SGLT2) inhibitor
	Percentage of patients with T2D and micro/macro-albuminuria being treated with angiotensin-converting-enzyme-inhibitor (ACE) or angiotensin-2-receptorantagonist (AT2)
	Percentage of patients with T2D and LDL > 2.5 mmol/L being treated with statins
Secondary clinical outcome measures	Percentage of patients with T2D and HbA1c < 58 mmol/L
	Percentage of patients with T2D and HbA1c < 53 mmol/L
	Percentage of patients with T2D and blood pressure < 140 mmHg
	Percentage of patients with T2D and blood pressure < 130 mmHg
	Percentage of patients with T2D and low-density lipoprotein > 2.5 mmol/L
	Percentage of patients with T2D and microalbuminuria and LDL > 1.8 mmol/L
Primary competence and organization outcome measures	The extent to which the GP is confident managing T2D in general
	The extent to which the GP is skilled in making decisions on T2D in general
	The extent to which the GP is confident managing T2D and ischemic heart disease, stroke, peripheral artery disease, and heart failure
	The extent to which the GP is confident managing T2D and blood pressure
	The extent to which the GP is confident managing T2D and kidney disease
	The extent to which the GP is confident managing T2D and cholesterol
Secondary competence and organization outcome measures	GPs rating of the degree of relational coordination within the general practice
	GPs rating of the degree of relational coordination with the endocrinology department

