### Sample and power calculation

The pragmatic nature of the RCT means that the sample size is determined by two contextual circumstances: a formal agreement with PLO-Aarhus and PLO-M to run the study in Aarhus Municipality (cf. above) where the total population of general practices was 100 and the fact that Danish general practices operate as private firms and thus decide themselves if they want to participate in a project. Based on these circumstances along with the study team’s research experiences with recruiting general practices, we used opinion-seeking to derive at the number of 30 general practices that were expected to participate.

We calculated the power for finding a significant difference between the intervention and control group on the three primary clinical outcomes using data from Danish registries and opinion-seeking within the study team. Additional file 5 shows the key parameters and the STATA command we used to calculate the following three power values:Power of 0.8870 for Primary clinical outcome 1: Percentage of patients with T2D and ischemic heart disease and/or stroke being treated with GLP1-RA and SGLT2 inhibitorPower of 0.9941 for Primary clinical outcome 2: Percentage of patients with micro/macro-albuminuria being treated with ACE or AT2Power of 0.9848 for Primary clinical outcome 3: Percentage of patients with LDL > 2.5 mmol/L being treated with Statins.

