### Statistical analysis plan

Statistical significance is expressed in 95% two-sided confidence intervals. A *p*-value of < 0.05 will indicate statistical significance.

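### Power of 0.8870–0.9941 is quoted with no significance level, and the article gives two conflicting thresholds (0.05 and 0.0167) that both cover the three primary clinical outcomes

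*Protocol article*

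**What the plan says.** Four places in the protocol article bear on this.

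- **Abstract, Methods.** The design is said to allow detection of "a significant difference between the intervention (*n* = 15) and control group (*n* = 15") "regarding the three primary clinical outcomes with a power of 0.8870–0.9941". No significance level is given.
- **Sample and power calculation.** "We calculated the power for finding a significant difference between the intervention and control group on the three primary clinical outcomes", followed by 0.8870 for outcome 1 (GLP1-RA and SGLT2 inhibitor), 0.9941 for outcome 2 (ACE inhibitor or AT2 antagonist) and 0.9848 for outcome 3 (statins). Again no level is given. The parameters and the Stata command are in Additional file 5, which is not at hand.
- **Outcomes, Clinical outcomes.** A Bonferroni correction is applied, "which means we only reject the null hypothesis of a primary clinical outcome if the" p "value is less than 0.0167 (i.e., 0.05/3").
- **Statistical analysis plan.** Significance is expressed through two-sided 95% confidence intervals, and a p-value "of < 0.05 will indicate statistical significance". The three primary clinical outcomes are not excepted.

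**The concern.** The last two rules overlap. A primary clinical outcome with p between 0.0167 and 0.05 would be significant under the Statistical analysis plan section, and its 95% interval would exclude no difference. Under the Clinical outcomes section its null hypothesis would not be rejected.

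The power statements inherit this ambiguity, because they are worded in terms of a significant difference and say nothing of the level. That matters most for outcome 1, which has the lowest stated power. A reader who takes 0.8870 at face value will treat a null result there as having about an 11% chance of missing the planned effect (1 − 0.887 = 0.113). If that figure belongs to a test at 0.05, the chance at the threshold that decides the outcome is about twice as large.

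The figures carry some weight. According to the Sample and power calculation section, the 30 practices came from expected participation and not from a power target, so the three power values are the article's quantitative support for that number being enough.

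**Working it through.** **Can the printed power be reproduced?** No. The event rates, effect sizes, cluster sizes, intra-cluster correlation and significance level are not in the article's text. What can be done is to take each printed power as given, recover the standardised effect it implies under an assumed level, and re-evaluate that effect at 0.0167.

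**Inputs**
- Stated power: 0.8870, 0.9941 and 0.9848 (Sample and power calculation).
- Practices: 15 + 15, giving 30 − 2 = 28 degrees of freedom for a comparison of practices (Abstract).
- Deciding threshold: 0.05/3 = 0.0167 (Clinical outcomes). The division is correct.
- Two-sided testing (Statistical analysis plan).
- *Assumption to be tested:* the printed power was calculated at two-sided 0.05.

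**Normal approximation throughout**

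Implied effect: δ = z(0.975) + z(power).

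Power at the new level: Φ(δ − z(1 − 0.05/6)), with z(0.975) = 1.960 and z(1 − 0.05/6) = 2.394.

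- Outcome 1: δ = 3.171; Φ(3.171 − 2.394) = 0.781
- Outcome 2: δ = 4.478; Φ(4.478 − 2.394) = 0.981
- Outcome 3: δ = 4.125; Φ(4.125 − 2.394) = 0.958

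**Noncentral t on 28 df throughout**

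The noncentrality is solved so that power at 0.05 equals the printed value (critical t 2.048), then power is recomputed at 0.05/3 (critical t 2.546).

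- Outcome 1: noncentrality 3.285; power 0.765
- Outcome 2: noncentrality 4.642; power 0.978
- Outcome 3: noncentrality 4.276; power 0.951

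Fewer degrees of freedom change little: outcome 1 is 0.763 with 26 df and 0.758 with 20 df.

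**The other assumption**

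If the printed values were already calculated at 0.0167, they need no correction. Outcome 1 would then have power of about 0.950 at 0.05.

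| Outcome | Printed | At 0.0167, if printed value used 0.05 | At 0.0167, if printed value used 0.0167 |
|---|---|---|---|
| 1 | 0.8870 | 0.76–0.78 | 0.8870 |
| 2 | 0.9941 | about 0.98 | 0.9941 |
| 3 | 0.9848 | 0.95–0.96 | 0.9848 |

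**The case against.** The strongest reply is that no printed number has been shown to be wrong. The article sends the reader to Additional file 5 for the parameters and command, and an article may leave such detail to a supplement. The Clinical outcomes section is also a definition of significance, and it is written for exactly these three outcomes. A specific rule normally overrides a general one, so significance in the power statements can be read as 0.0167 at least as naturally as 0.05. On the adverse reading, too, outcomes 2 and 3 remain well powered, and the sample size would not change.

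Most of this stands. A reader might infer that the power was calculated at 0.05 and that the headline is therefore overstated. The article does not establish this, so the lower figures must remain conditional.

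A reader might also arrive at 0.73 for outcome 1. That value (0.730) appears only if 0.887 is taken as a normal-approximation figure at 0.05 and the test is then a t test on 28 df. On that mixture, power at 0.05 is already 0.864, so part of the fall comes from the change of reference distribution and not from the Bonferroni threshold. The article does not fix a t reference for these outcomes. Like for like, the range is 0.76–0.78.

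The reply does not remove the overlap. The 0.05 rule and the 95% intervals are stated without exception and disagree with the Bonferroni rule for the same outcomes. Nor does a supplement repair an abstract that gives power without saying at what level it holds.

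**Conclusion.** The article gives two significance thresholds that both cover the three primary clinical outcomes, and quotes power for them without saying which applies. This is visible in the text and needs no assumption.

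The size of the consequence does depend on an assumption. If the level was two-sided 0.05, the planned effect on outcome 1 would be missed with probability of about 22–24% (1 − 0.781 = 0.219; 1 − 0.765 = 0.235) instead of 11%, and its power would be below 0.80. Outcomes 2 and 3 would still be at about 0.95 or more. If the level was already 0.0167, nothing is overstated and only the reporting needs correction. The text shown does not settle which case holds, so it would be wrong to call the headline power an arithmetic error.

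**What to change.** 1. In the Statistical analysis plan section, limit the 0.05 rule and the 95% intervals to outcomes other than the three primary clinical ones. Alternatively, state there that those three are judged at 0.0167 and reported with 98.33% intervals (1 − 0.05/3 = 0.9833).
2. Check the level used in the command in Additional file 5.
3. If it was 0.0167, keep the three values and print the level beside each of them in the Abstract and in Sample and power calculation.
4. If it was 0.05, rerun the three commands at 0.0167 and restate the power in both places, with the level beside each value.

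The cost is one check, at most three reruns and a few edited sentences. The number of practices and the design stay as they are. The one disadvantage is a less favourable stated power, chiefly for outcome 1, if the level was 0.05.

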**Discussion:**

The potential of virtual conferences is yet to be fully tapped because of methodological limitations. Studies have also not yet systematically evaluated virtual conferences in the context of chronic care using a high-quality research design. Given the nature of this real-life intervention, general practitioners and endocrinologists cannot be blinded to their allocation to either the intervention or comparison arm.

**Trial registration:**

ClinicalTrials.gov, United States National Institutes of Health trial ID: NCT05268081. Registered on 4 March 2022.

**Supplementary Information:**

The online version contains supplementary material available at 10.1186/s13063-022-06961-y.

## Introduction

### Background

Globally, 462 million people is estimated to live with type 2 diabetes (T2D). This corresponds to 6.3% of the world’s population, which makes T2D one of the most common chronic diseases [1]. In Denmark, 240,000 people (4.1%) are diagnosed with T2D, and by 2030, the number is projected to nearly double [2]. T2D elevates the risk of developing macro- and micro-vascular complications (e.g., atherosclerotic cardiovascular disease, chronic kidney disease and peripheral neuropathy) resulting in higher mortality, higher morbidity, increased disability, poorer quality of life [3], and a substantial economic burden for society in medical costs and reduced productivity [4]. The risk of developing complications can be considerably reduced if health care professionals help to secure optimal levels of lipids, blood pressure, and glycated haemoglobin by appropriate pharmacological treatment to supplement life-style interventions [3, 5]. However, management of T2D is a complex task since it is often accompanied by other diseases (e.g., heart or kidney failure) [6–8], which requires the use of several different and sometimes interacting drugs. Furthermore clinical guidelines are revised regularly as new knowledge and new pharmaceuticals emerge at a rapid pace [9, 10]. Unfortunately, these care challenges have led to a wide gap between the recommended pharmacological care and the care that patients receive, both internationally and in Denmark [11–13]. Thus, it is urgent to improve the pharmacological management of patients living with T2D.

In Denmark, most patients with T2D are treated and followed by their general practitioner (GP). Hospital-employed endocrinologists provide written support and phone counselling to GPs regarding treatment of patients with T2D. To support GPs in providing high quality care of T2D, literature reviews emphasize the need for implementing models of collaboration that in a simple and effective way facilitate clinical dialogue between GPs and endocrinologists [3, 14]. Previous studies have tried various quality improvement strategies targeting health care providers or the organization of health care delivery, of which the latter is found to have the largest effect on disease management [15, 16]. Presently, virtual conferences are being tested across healthcare systems as a new way connecting hospitals and general practices [17–21] because of its potential to improve treatment, increase competences in general practice, and provide cost-effective health care [22]. This potential, nevertheless, is yet to be fully tapped and studied because of methodological limitations such as lacking a control group or an adequately powered multi-group trial [15]. Moreover, studies have not systematically tested and evaluated virtual conferences in the context of chronic care using a high-quality research design [14] or done it by studying the effect on clinical endpoints and competences in general practice [23]. A prospective study suggests that cross-sectoral virtual conferences about T2D care improve metabolic and hemodynamic parameters after 1 year [24].

The aim of the project is to evaluate if virtual specialist conferences between endocrinologists and general practitioners about patients living with T2D is clinically effective and improves diabetes competences and organization in general practice in comparison to usual practice. This aim will be studied in a pragmatic randomized controlled trial design that maximizes external validity, is tested in a wide range of participants, and measures important clinical outcomes [25]. Since our intervention will influence the general practice as a whole, it will be the unit of randomization. The intervention was developed using the Medical Research Council (MRC) Framework [26, 27]. The project also studies factors that facilitate or limit the implementation of cross-sectoral and virtual specialist conferences [28], which are important to understand for subsequent upscaling [18]. The project will provide new and clinically relevant knowledge on how to manage the increasing number of persons with T2D seen in general practice.

### Study aim and objectives

The overall aim of the project is to evaluate if virtual specialist conferences between endocrinologists and general practitioners about patients living with T2D is clinically effective and improves diabetes competences in general practice in comparison to usual practice. We distinguish between clinical objectives and competence and organization objectives in the following ways.

The primary clinical objective is to study if the intervention group compared to general practices receiving usual practice is superior in improving the percentage of patients with T2D and three types of co-morbidities on appropriate diabetes related medication:Ischemic heart disease and/or stroke being treated with glucagon-like peptide 1 receptor agonists (GLP1-RA) and sodium glucose cotransporter 2 (SGLT2) inhibitorMicro/macro-albuminuria being treated with Angiotensin-converting-enzyme-inhibitor (ACE) or angiotensin-2-receptorantagonist (AT2)Low-density lipoprotein (LDL) > 2.5 mmol/L being treated with Statins.

The secondary clinical objective is to study if the intervention group compared to the control group decreases the percentage of patients with type 2 diabetes and respectively:HbA1c < 58 mmol/LHbA1c < 53 mmol/LBlood pressure < 140 mmHgBlood pressure < 130 mmHgLDL > 2.5 mmol/LLDL > 1.8 mmol/L

The primary diabetes competence and organization objective is to study if general practitioners’ in the intervention group compared to the control group self-reports a higher degree of:Confidence and skills in managing type 2 diabetes in generalConfidence in managing type 2 diabetes and cardiovascular disease or heart failureConfidence in managing type 2 diabetes and blood pressureConfidence in managing type 2 diabetes and kidney diseaseConfidence in managing type 2 diabetes and cholesterol.

The secondary diabetes competence and organization objective is to study if the intervention group compared to the control group self-reports a higher assessment of:General practitioners’ rating of relational coordination in the general practiceGeneral practitioners’ rating of relational coordination with the hospitalGeneral practitioners’ rating of using virtual conferencesPractice staffs’ rating of relational coordination in the general practicePractice staffs’ rating of relational coordination with the hospitalPractice staffs’ rating of using virtual conferencesPractice staffs’ confidence in managing type 2 diabetes in generalPractice staffs’ confidence in managing type 2 diabetes and cardiovascular disease or heart failurePractice staffs’ confidence in managing type 2 diabetes and blood pressurePractice staffs’ confidence in managing type 2 diabetes and kidney diseasePractice staffs’ confidence in managing type 2 diabetes and cholesterol

### Trial design

A prospective, pragmatic, and superiority RCT with two parallel arms of general practices. General practices will be randomized to the virtual conference intervention or usual care arm with 1:1 allocation, stratified by the type of general practice to ensure a balanced allocation. Additional file 1 reports the trial according to the *Standard Protocol Items: recommendations for Interventional trials* (SPIRIT) statement [29]. Figure 1 shows the study flow chart.

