#### Difference between intervention and control group

The main analysis concerns the difference between the intervention and control group at month 12. Data from the Diabetes Overview and general practice survey are analysed using simple, multiple, and logistic regression analyses. Analysis is done according to the intention-to-treat principle to test if the groups differ in terms of outcome measures. The analysis of survey data will take into account cluster effects using the intra-cluster correlation coefficient. Using *t*-test and *Χ*^2^ tests, depending on the outcome measure, it will be determined if randomization has resulted in systematically different groups. Survey data are tested to determine if questions or indices of questions are internally consistent (Cronbach alpha). In the regression analyses, control variables at the individual (e.g., seniority) and practice level (e.g., form and size of practice) are tested to determine its influence on survey outcomes.

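### The stratification factors are stated in two different ways, and the analysis text does not commit to including them in the primary clinical models

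*Protocol article*

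**What the plan says.** The article describes the randomisation scheme twice. The Trial design section says that allocation is 1:1 and "stratified by the type of general practice to ensure a balanced allocation"; type is not defined. The Assignment of interventions section says "Block randomization is performed at the general practice level" and then "Randomization included stratification by number of full-time GPs and geographic location". It gives a reason for the second factor: "general practices located in the centre and periphery of the municipality of Aarhus differ in patient demographics".

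The Sample and power calculation section expects 30 practices, and the abstract gives 15 per arm. Under Clinical outcomes, each of the three primary clinical outcomes is tested at 0.0167.

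The analysis text is in the section Difference between intervention and control group: "Data from the Diabetes Overview and general practice survey are analysed using simple, multiple, and logistic regression analyses". The only covariates it names are seniority at the individual level and practice form and size at the practice level. It says that they "are tested to determine its influence on survey outcomes". No covariate is named for the clinical outcomes, and location is not named for any outcome.

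**The concern.** A reader cannot tell from the article how practices were allocated. There may be one factor or two, and location may or may not be among them. The scheme determines which factors the analysis should carry, so the discrepancy affects more than wording.

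The analysis section does not close the gap. The one factor for which the article argues a prognostic role, location, is absent from it. Practice size appears, but only for survey outcomes and as something to be tested.

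Stratified allocation makes the arms alike on the strata. A model that leaves the strata out still counts the differences between them as noise, so its standard error exceeds the true variability of the estimate. With about 30 practices, that costs power that could be had at little expense.

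**Working it through.** **Setting the texts side by side.** Trial design gives one factor, type of practice. Assignment of interventions gives two, number of full-time GPs and location. If type means solo versus partnership, it could be loose wording for number of GPs. It would still not cover centre versus periphery, which the second section justifies separately. The two descriptions therefore differ in both number and content.

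**Inputs from the article.** 15 + 15 practices; significance level 0.05/3 = 0.0167, which reproduces; stated power of 0.8870 for primary clinical outcome 1. The rates, intra-cluster correlation, cluster size and effect behind that power are in Additional file 5, which is not shown, so the stated power cannot be reproduced.

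**Assumptions.** The stated power was computed at 0.0167. Analysis is linear, on one result per practice. There are four strata of 8, 8, 8 and 6 practices, each split evenly between arms. Strata explain a share R² of the total variance of practice-level results, varied from 0 to 0.5.

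**Implied effect.** With the practice-level SD set to 1, the normal approximation gives d = (2.394 + 1.211) × √(2/15) = 3.605 × 0.3651 = 1.316.

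**Simulation.** 40,000 runs per setting compared a t-test ignoring strata with a linear model including stratum indicators, both at nominal 0.0167.

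| R² | Type I error, strata ignored | Type I error, adjusted | Power, strata ignored | Power, adjusted | Gain (points) |
|---|---|---|---|---|---|
| 0 | 0.0165 | 0.0168 | 0.849 | 0.843 | −0.6 |
| 0.1 | 0.0116 | 0.0162 | 0.858 | 0.882 | 2.4 |
| 0.2 | 0.0076 | 0.0168 | 0.868 | 0.920 | 5.2 |
| 0.3 | 0.0041 | 0.0168 | 0.881 | 0.952 | 7.1 |
| 0.5 | 0.0008 | 0.0171 | 0.908 | 0.992 | 8.4 |

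The first row shows 0.849 rather than 0.887 because the simulation uses the t distribution, while d was solved with normal quantiles.

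**What happens to precision.** At R² = 0.2 the true SD of the estimate is 0.327 under both analyses. The mean reported standard error is 0.364 when strata are ignored and 0.323 when they are included. The balance is kept; only the reported uncertainty is inflated.

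**Check by formula.** The type I error ignoring strata is 2 × (1 − Φ(2.394/√(1 − R²))). This gives 0.0116 at R² = 0.1 and 0.0042 at R² = 0.3, in agreement with the table. The standard error ratio 1/√(1 − R²) is 1.054 and 1.195.

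**If the share applies to between-practice variance only.** A practice percentage also carries within-practice sampling variance, which practice-level strata do not remove. With an assumed intra-cluster correlation of 0.05 and 30 eligible patients per practice, between-practice variance is 0.05/(0.05 + 0.95/30) = 0.61 of the total. Shares of 10% and 30% become 0.061 and 0.184 of the total. The standard error ratio is then 1.03 to 1.11, and the type I error 0.0135 to 0.008. By the table, the gain at 0.061 lies below 2.4 points and the gain at 0.184 between 2.4 and 5.2. Over assumed correlations of 0.02–0.10 and 15–60 patients, the standard error inflation is 1–5% for a 10% share and 4–16% for a 30% share.

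**The case against.** The strongest objection is that the article never says the clinical analysis is unadjusted. It lists multiple regression for the Diabetes Overview data, which implies covariates, and a journal article may leave their list to a fuller plan. This stands. A reader might infer that the primary analysis adjusts for neither set of factors, but that is an inference from silence. What can be said is that the article makes no commitment, and that the only covariates it does name belong to the survey outcomes.

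A reader might also infer that the precision bought by stratification is thrown away. The simulation contradicts this: the true SD of the estimate is the same either way.

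The size of the effect can be challenged too. The explained share is assumed, and applying it to the total variance gives the upper end. The standard error formula belongs to a linear practice-level analysis and does not carry over to the logistic regression that the article also lists. These limits stand, and the figures are illustrations.

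Saying that covariates are tested need not mean that they are selected on the result, since no selection rule is stated, and the sentence concerns survey outcomes. This also stands in part: the wording leaves data-driven selection open but does not establish it.

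Finally, Trial design may be a one-line summary, with Assignment of interventions as the governing text. That is plausible, but it does not remove the discrepancy, because type of practice is not a natural summary of location.

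**Conclusion.** The inconsistency between Trial design and Assignment of interventions is on the page and needs correcting. Prespecifying the strata in the between-arm models is a sound and nearly free improvement.

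If strata explain 10–30% of the total variance of practice-level results, ignoring them takes the type I error from 0.0167 to about 0.012–0.004, and including them gains about 2–7 power points. The gain is smaller if the share refers to between-practice variance. If the strata are not prognostic, including them costs one point or less (0.6 in the simulation). The result rests on the assumed share, on balanced strata, on a linear practice-level analysis and on the stated power having been computed at 0.0167.

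Ignoring the strata would make the test conservative, so this is not a threat of false positive findings. Nor do the documents show that the analysis will depart from the allocation scheme, since they state no analysis strata at all.

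**What to change.** 1. State one set of stratification factors, with the categories of each, in both Trial design and Assignment of interventions. It must match the allocation list actually generated; the article alone does not settle which description that is.
2. Include those factors as prespecified fixed covariates in every between-arm model, including those for the three primary clinical outcomes.
3. Use this set in place of covariates chosen by testing, and reword the sentence on control variables accordingly. Keep the number of categories small for 30 practices.

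The change is one of wording. The factors are known for every practice before randomisation, so no new data are needed. An unadjusted comparison of 30 practices has 30 − 2 = 28 degrees of freedom. Two binary factors entered separately use 2 of them, and four stratum indicators use 3. Recruitment was still under way when the article was submitted, so at that stage the change could be made before the month-12 analysis.
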